# Rapamycin and inulin for booster vaccine response stimulation (RIVASTIM)—rapamycin: study protocol for a randomised, controlled trial of immunosuppression modification with rapamycin to improve SARS-CoV-2 vaccine response in kidney transplant recipients

**DOI:** 10.1186/s13063-022-06634-w

**Published:** 2022-09-15

**Keywords:** Kidney transplantation, Randomised controlled trial, Sirolimus, Immunosuppression, SARS-CoV-2, COVID-19, Vaccination

## Abstract

Kidney transplant recipients are at an increased risk of severe COVID-19-associated hospitalisation and death. Vaccination has been a key public health strategy to reduce disease severity and infectivity, but the effectiveness of COVID vaccines is markedly reduced in kidney transplant recipients. Urgent strategies to enhance vaccine efficacy are needed.

**Methods:** RIVASTIM-rapamycin is a multicentre, randomised, controlled trial examining the effect of immunosuppression modification prior to a third dose of COVID-19 vaccine in kidney transplant recipients who have failed to develop protective immunity to a 2-dose COVID-19 vaccine schedule. Participants will be randomised 1:1 to either remain on standard of care immunosuppression with tacrolimus, mycophenolate, and prednisolone (control) or cease mycophenolate and commence sirolimus (intervention) for 4 weeks prior to and following vaccination. The primary outcome is the proportion of participants in each trial arm who develop protective serological neutralisation of live SARS-CoV-2 virus at 4–6 weeks following a third COVID-19 vaccination. Secondary outcomes include SARS-CoV-receptor binding domain IgG, vaccine-specific immune cell populations and responses, and the safety and tolerability of sirolimus switch.

**Discussion:** Immunosuppression modification strategies may improve immunological vaccine response. We hypothesise that substituting the mTOR inhibitor sirolimus for mycophenolate in a triple drug regimen will enhance humoral and cell-mediated responses to COVID vaccination for kidney transplant recipients.

**Trial registration:** Australia New Zealand Clinical Trials Registry ACTRN12621001412820. Registered on 20 October 2021; https://www.anzctr.org.au/Trial/Registration/TrialReview.aspx?id=382891&isReview=true

## Administrative information

Note: the numbers in curly brackets in this protocol refer to SPIRIT checklist item numbers. The order of the items has been modified to group similar items (see http://www.equator-network.org/reporting-guidelines/spirit-2013-statement-defining-standard-protocol-items-for-clinical-trials/).

## Introduction

### Background and rationale {6a}

Kidney transplant recipients (KTRs) are at an increased risk of COVID-19 associated morbidity and mortality, with the combined effects of immunosuppression and prevalent comorbidities contributing to the high rates of adverse outcomes [1, 2]. Meta-analyses have suggested a 28-day mortality approaching 25% for KTRs positive for SARS-CoV-2, and survivors have significant risk of morbidity including hospitalisation, acute kidney injury, and graft loss [2].

The development of effective vaccines which target the SARS-CoV-2 spike protein has been crucial to reducing disease burden and the development severe COVID-19 disease [3]. However, immunocompromised populations such as KTRs were excluded from initial vaccine trials. KTRs exhibit suboptimal vaccine responses and are inadequately protected by current standard two- and three-dose vaccine regimes [4, 5].

To address the inadequate vaccine response observed in KTRs and other immunocompromised groups, additional doses of mRNA vaccine have been recommended. In KTRs, data from a randomised controlled trial suggest that a third mRNA vaccine dose increases the proportion of patients with protective neutralising antibodies to 60%, compared to 25% in the placebo group [6]. While a third vaccine dose improves vaccine immunogenicity, to what extent seropositive patients are protected is unclear, and a significant minority of KTRs fail to seroconvert and therefore require additional strategies [6–8].

Observational data suggests that vaccine responses are significantly affected by immunosuppression regimen. The use of mycophenolate has been identified as a key factor associated with vaccine hypo-responsiveness [5]. Such observations are consistent with earlier reports identifying mycophenolate use as being strongly associated with infection risk among maintenance-phase KTRs, and that use of mycophenolate was associated with inadequate responses to influenza vaccination [9–12]. Conversely, mechanistic target of rapamycin inhibitors (mTORi) have been found to boost vaccine-elicited cytotoxic T cell memory responses in non-human primates, and to improve antibody responses to influenza vaccination in elderly individuals [13, 14]. A recent, multicentre study of over 2000 KTRs reported a 50% reduction in viral infections among KTRs randomised to an mTORi-based regimen, as compared to those receiving mycophenolate, calcineurin inhibitor, and steroid [15, 16].

These observations led to recognition of mTOR complex 1 (mTORC1) activity as a key determinant of the effector versus memory fate decision of antigen-experienced T cells following vaccination [17, 18]. Sirolimus is a potent inhibitor of mTORC1, and the use of mTOR inhibitor-based immunosuppressive protocols has been associated with superior rates of seroconversion, as well as greatly enhanced T cell mediated immunity against SARS-CoV-2 spike protein [19]. Vaccine responses may also be modulated by commensal gastrointestinal microorganisms, collectively the microbiome [20–23]. mTOR inhibitors such as sirolimus have been associated with immunosuppression-regimen-specific changes in the microbiome [24, 25], which may play a role in vaccine immune responses [26].

The RIVASTIM trials are designed to investigate potential strategies to enhance vaccine immunological responses in KTRs using supplementation of the pre-biotic inulin, or immunosuppression regimen alteration. RIVASTIM-Rapamycin is a multicentre, randomised, controlled trial of immunosuppression alteration in KTRs who have failed to develop vaccine-induced protective immunity to COVID-19, prior to a third vaccination. We hypothesise that cessation of mycophenolate and commencing sirolimus in a 3-drug regimen (tacrolimus, sirolimus, prednisolone) will improve the immune response to a third mRNA COVID-19 vaccine.

### Objectives {7}

The primary objective is to compare the proportion of participants in each trial arm who develop protective serological neutralisation of live SARS-CoV-2 virus (ancestral strain) at 4–6 weeks following a third COVID-19 vaccination. The secondary objectives are to determine whether the sirolimus switch (1) improves the proportion of patients that achieve protective anti-receptor binding domain (RBD) IgG antibody, (2) improves the magnitude of vaccine induced T cell response, and (3) is safe and well-tolerated.

### Trial design {8}

RIVASTIM-rapamycin is a multicentre, parallel-arm, randomised, controlled, superiority trial, seeking to examine the effect of ceasing mycophenolate and commencing sirolimus in a 3-drug regimen on the immune response to a third dose of mRNA COVID-19 vaccine in kidney transplant recipients who have failed to demonstrate protective immunity following a two-dose vaccine schedule. KTRs on triple therapy who have received 2-doses of a COVID-19 vaccine will be enrolled and their immune response to vaccination assessed by measurement of serological anti-RBD IgG titre. Those with a satisfactory immune response (anti-RBD IgG ≥ 100 U/mL) will exit the study and be advised to receive a third mRNA COVID-19 vaccination as per recommended guidelines. KTRs who fail to demonstrate protective immunity (anti-RBD IgG <100 U/mL) will proceed to randomisation.

Randomisation will occur at a participant level with an allocation ratio of 1:1, stratified by study site and the magnitude of immune response following 2 doses of vaccine (anti-RBD IgG titre; non-responder: < 0.4 U/mL; low responder: 0.4–99 U/mL). An outline of the trial is shown in Fig. 1. Following randomisation patients will either continue their usual immunosuppression regimen of tacrolimus, mycophenolate, and prednisolone (control arm), or have mycophenolate ceased and sirolimus commenced (intervention arm). Sirolimus will be commenced at a standard dose of 2mg daily, with target trough levels of 6 ng/mL and weekly dose titration. Tacrolimus dosage will be adjusted to achieve trough concentration within a range of 3–6 ng/mL. Following a 4-week lead in period, participants will receive a third dose of mRNA COVID-19 vaccine, with the subsequent antibody response measured at 4–6 weeks post vaccination. Participants will continue immunosuppression as per group at least until the time of antibody assessment, and thereafter as determined by their usual nephrologist. The first study participant was enrolled on the 8 November 2021 and recruitment continued through to 15 February 2022, with the final study visit of the last recruited patient in April 2022.

**Fig. 1 Fig1:**
[figure not shown]
Outline of the trial

## Methods: participants, interventions, and outcomes

### Study setting {9}

The trial will be conducted at the renal transplant units of two tertiary referral hospitals in Australia: (1) The Royal Adelaide, Hospital, Adelaide, South Australia, and (2) The Royal Prince Alfred Hospital, Sydney, New South Wales.

### Eligibility criteria {10}

The inclusion criteria are:Kidney transplant recipientsAged 18–75 yearsEstimated GFR >25 mL/minSpot urinary albumin to creatinine ratio <100 mg/μmolCurrent immunosuppression regimen comprising tacrolimus, mycophenolate, and prednisoloneTreating nephrologist agrees that patient is suitable for sirolimus maintenance immunosuppressionHave received 2 doses of a COVID-19 vaccine regimen (either adenoviral vector or mRNA-based) and have demonstrably not responded (anti-spike RBD IgG antibody titre below 100 U/mL)

The exclusion criteria are:Aged <18 years or >75 yearsSignificant kidney dysfunction, estimated GFR ≤25 mL/min or spot urinary albumin to creatinine ratio ≥100 mg/μmolUnable or unwilling to provide informed consent to participate in the trialHave received 2 doses of a COVID-19 vaccine regimen (either adenoviral vector or mRNA-based) and have mounted an adequate immune response (anti-spike RBD IgG antibody titre above 100U/mL)Have had documented infection with COVID-19 and/or have detectable SARS-CoV-2 nucleocapsid-specific IgGKnown allergy to or intolerance of sirolimus or everolimus

### Who will take informed consent? {26a}

The patient’s treating nephrologist will determine participant eligibility and approach the patient regarding their interest in participating in the clinical trial. Trained research staff will then discuss the trial, provide written information, and seek informed consent during a scheduled clinic appointment. All clinical and research staff involved in consent and enrolment have received trial-specific training and adhere to Good Clinical Practice (GCP) requirements.

### Additional consent provisions for collection and use of participant data and biological specimens {26b}

Participants will provide informed consent to the sampling of biological material (blood and stool), which will be deidentified and stored in the secure research facilities of the participating trial sites and may be used for future studies. Consent for the genomic sequencing of stool microbiota is addressed, with the understanding that no human genomic information will be collected.

### Interventions

#### Explanation for the choice of comparators {6b}

Standard of care immunosuppression for transplant patients consists of a calcineurin inhibitor (CNI, most commonly tacrolimus), an antimetabolite (most commonly mycophenolate), and a corticosteroid (prednisolone/prednisone) [27]. Mycophenolate has been associated with suppressed humoral vaccine response, while sirolimus is associated with improved humoral and cellular vaccine response [19]. There is less risk of acute rejection when replacing mycophenolate with sirolimus, as opposed to replacing CNI with sirolimus [28]. When sirolimus is used in combination with tacrolimus, lower target concentrations of tacrolimus can be used to minimise treatment-related adverse events [28].

#### Intervention description {11a}

Participants will be randomly allocated to their inclusion in one of two groups:Continuation of current immunosuppression regimen including mycophenolate, available in the form of mycophenolate sodium or mycophenolate mofetilCessation of mycophenolate, and commencement of rapamycin, available as sirolimus (Rapamune®, Pfizer Australia Pty Ltd)

The study products will be provided through the patients’ elected pharmacy. Control arm participants will continue their usual immunosuppression regimen as directed by their treating nephrologist, with standard target trough tacrolimus levels in our institutions ranging from 5 to 8 ng/mL [29]. Intervention arm participants will cease mycophenolate the day prior to commencing sirolimus 2mg daily. Trough drug levels will be taken at days 5–7 with dose titration targeting trough level 6 ng/mL and ongoing weekly levels to ensure stabilisation prior to vaccination.

All trial participants will receive a third “booster” dose of a COVID-19 mRNA vaccine, either Pfizer-BioNTech BNT162b2 (30 μg, IM) or Moderna mRNA-1273 (50 μg, IM) determined by local practice and vaccine availability. Study participants will receive written pre-vaccination information on the benefits and potential risks and harms of the COVID-19 vaccine and be screened for contraindications to immunisation such as serious adverse events attributable to a previous dose of a mRNA COVID-19 vaccine. All patients will be advised of the need to continue with additional public health measures (i.e. physical distancing, hand washing, wearing a face mask, and COVID-19 testing and isolation as required).

#### Criteria for discontinuing or modifying allocated interventions {11b}

Sirolimus has known dose-related adverse effects (AEs). Trough level targets of 6 ng/mL are generally well tolerated [30]. Participants who experience severe adverse events will cease sirolimus and return to their usual immunosuppression regimen. Participants who experience mild AEs related to sirolimus trough levels above target will have their dose reduced. Participants who continue to experience mild AEs (mouth ulcers, peripheral oedema) at target trough level will be offered the option of discontinuing the study intervention and continuing with trial follow-up.

#### Strategies to improve adherence to interventions {11c}

RIVASTIM-rapamycin uses the combination of tacrolimus and sirolimus to facilitate lower target sirolimus and tacrolimus exposure without an increase in the risk of graft rejection [28]. This reduces the likelihood of sirolimus-associated adverse events which are generally dose-related. Following randomisation, participants in the intervention arm will have weekly blood tests for dose titration and to ensure adequate adherence.

### Relevant concomitant care permitted or prohibited during the trial {11d}

All participants will continue with usual transplant management as per local standard of care and at the discretion of their treating nephrologist. Any changes to medications will be recorded. Participants will be asked to continue with their usual diet and medications.

### Provisions for post-trial care {30}

Following completion of the trial intervention, patients will be contacted within 1 week to monitor for adverse events. In conjunction with their treating nephrologist, patients will be offered continuation of the trial drug regimen or return to their previous immunosuppression regimen. Patients converting back to mycophenolate will have this arranged by the trial team, with usual post-transplant care and follow-up then continuing per routine practice under the guidance of the treating nephrologist. The trial sponsor has indemnity to compensate those who suffer from potential harm from as a result of their participation in the research study.

### Management of COVID-19-positive participants during the trial

Study participants who returned a positive COVID-19 result during the trial will be managed in consultation with their treating transplant unit as per local best practice. Participants who contract COVID-19 following randomisation but prior to a third vaccination may have their third vaccine dose delayed. Where possible, participants will be asked to continue with their allocated treatment regimens and attend study visits and follow-up. Positive COVID cases will be excluded from the primary analysis as SARS-CoV-2 infection will confound assessment of the primary outcome measure.

### Outcomes {12}

#### Primary outcome measure

The primary outcome is the proportion of participants in each trial arm who develop protective serological neutralisation of live SARS-CoV-2 virus (ancestral strain) at 4–6 weeks following a third COVID-19 vaccination. The protective level is defined as 20.2% of the mean neutralisation level of a standardised cohort of COVID-19 convalescent individuals. This threshold correlates with 50% protection from infection with SARS-CoV-2 (ancestral strain) in the general population [31].

#### Secondary outcome measures

The secondary outcome measures include the following:2.The proportion of participants in each trial that reach a threshold of serological anti-SARS-CoV-2 (ancestral strain) RBD IgG antibody ≥ 100 units/mL (measured with an Elecsys Anti-SARS-CoV-2 immunoassay [Roche], and equivalent to 100 BAU/mL). This RBD IgG threshold was chosen on the basis of pre-clinical and clinical studies and is consistent with the reported outcomes in published COVID-19 clinical vaccine trials [6].3.The development of COVID-19 following randomisation, determined by:Positive SARS-CoV-2 PCR test, or rapid antigen test in the setting of symptomatic diseaseDetection of SARS-CoV-2 anti-nucleocapsid antibodies at the time of primary outcome assessment.4.Change in the median magnitude of the SARS-CoV-2 spike-specific, antiviral T cell response prior to and at 4–6 weeks following vaccination, determined as the frequency of cells that secrete IFNγ in response to stimulation with spike-protein (ancestral strain)-derived peptides.5.Phenotypic and functional characterisation of T and B lymphocyte populations6.Tolerance of sirolimus as determined by drug cessation, drug adherence, and drug-related adverse events including proteinuria, anaemia, leukopenia, rash, mouth ulcers, and pneumonitis.7.Adverse events following immunisation (AEFI) including adverse events of special interest (AESI) will be assessed via phone consultation at 1 week, and again at 4–6 weeks post-vaccination during the final follow-up visit, and include:Changes in kidney allograft function, determined by serum creatinine, eGFR (CKD-EPI equation), and proteinuriaThe occurrence of biopsy proven acute allograft rejectionThe recurrence of primary kidney diseasePatient-reported quality of life as recorded by the EQ-5D questionnaire8.Changes in the community structure, relative abundance, and functional characteristics of the gut microbiome following 4 weeks of sirolimus intervention, determined by 16S-rRNA metagenomic sequencing of participant stool samples.

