## Assignment of interventions: blinding

### Who will be blinded {17a}

Given the significant changes in prescribed immunosuppression, neither the study participants nor clinical staff will be blinded to treatment allocation. Scientific staff performing the laboratory assays for primary and secondary outcomes will be blinded to patient treatment allocation.

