### Adverse event reporting and harms {22}

All protocol deviations and AEs will be documented, regardless of their potential relationship to the study intervention. AEs will be recorded using an adaptation of the National Institute of Health’s Common Terminology Criteria for Adverse Events by a study team member on an eCRF. Recorded information on each AE will include a descript of the AE, the onset date, duration, the resolution of the AE, the severity and seriousness, any action taken as a result of the AE, the outcome of the AE, and the likelihood of the relationship of the AE to a study intervention. Screening for adverse events will occur during each study visit and during scheduled clinical follow-up with their treating nephrologist and will be captured up to 7 days following the final study visit. Adverse events following immunisation (AEFIs) with the exception of mild and/or short-lived symptoms will be reported to the Therapeutic Goods Administration (TGA). Serious adverse events (SAEs) will be reported to the trial sponsor with 24-h of the study team being made aware of the event.

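### The sirolimus tolerance outcome is defined in one arm and through drug-related events, so it does not use the randomised control or the all-cause adverse event data already collected to answer the safety objective

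*Protocol article*

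**What the plan says.** Under Objectives {7}, "The secondary objectives are to determine whether the sirolimus switch" introduces three aims. The third is that the switch "is safe and well-tolerated".

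Under Secondary outcome measures, item 6 gives the matching outcome: "Tolerance of sirolimus as determined by drug cessation, drug adherence, and drug-related adverse events", "including proteinuria, anaemia, leukopenia, rash, mouth ulcers, and pneumonitis".

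On blinding, section {17a} states that "neither the study participants nor clinical staff will be blinded to treatment allocation". Only the laboratory is masked: "Scientific staff performing the laboratory assays for primary and secondary outcomes will be blinded to patient treatment allocation".

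On data collection, section {22} is broad: "All protocol deviations and AEs will be documented, regardless of their potential relationship to the study intervention". A study team member records each event, and the record includes "the likelihood of the relationship of the AE to a study intervention". Recording continues to 7 days after the final visit and is not limited to one arm.

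**The concern.** The randomised intervention is a switch: mycophenolate stops and sirolimus starts. Whether the switch is safe and well tolerated is therefore a question about the difference from staying on mycophenolate. Item 6 instead describes one drug in the arm that receives it.

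Three things can go wrong if the outcome is followed as written.

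- Background events in the sirolimus arm have no control rate beside them. They are either charged to sirolimus or dismissed, depending on attribution.
- Events avoided by stopping mycophenolate cannot appear, because a one-arm count cannot show a reduction.
- If drug-related means judged related case by case, a judgement made with knowledge of the allocation becomes part of the outcome definition. It could move the count in either direction.

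This matters for how the trial is used. The Discussion says that improved immunity would strongly justify the switch, and it describes sirolimus as well tolerated. That recommendation needs the harms of the switch set against those of the control regimen.

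**Working it through.** The plan states no figure on this point, so there is none to reproduce. The check is mainly a comparison of sections, followed by an illustration with assumed rates.

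**Step 1: which arm each component of item 6 can occur in.**

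| Component | Sirolimus arm | Control arm |
|---|---|---|
| Sirolimus cessation | yes | not defined |
| Sirolimus adherence | yes | not defined |
| Sirolimus-related events | yes | not defined |
| The six named events, any cause | yes | yes, but not what item 6 counts |

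The primary outcome, by contrast, is worded as a proportion in each trial arm.

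**Step 2: whether item 7 fills the gap.** Item 7 covers kidney function, rejection, disease recurrence and quality of life, and is not tied to sirolimus. It is framed as events following immunisation, assessed 1 week and 4–6 weeks after the vaccine. As worded it does not clearly cover the 4-week lead-in, when sirolimus is started and titrated. Of the six events in item 6, only proteinuria reappears. The other five (anaemia, leukopenia, rash, mouth ulcers, pneumonitis) have no stated between-arm outcome.

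**Step 3: who attributes.** Section {17a} masks assay staff only. Section {22} has a study team member record each event, including its likely relationship to the intervention, and describes no masked review. Three of the six events (proteinuria, anaemia, leukopenia) are laboratory-measured, so their occurrence is less open to judgement than their attribution.

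**Step 4: illustration.** The planned size is 60 per arm (Sample size {14}). The event rates are assumptions, since the protocol gives none. Count = rate × 60.

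| Assumed leukopenia, sirolimus vs control | Count item 6 could report | Randomised difference |
|---|---|---|
| 10% vs 10% (6/60 vs 6/60) | 0 to 6 | 0 points |
| 5% vs 10% (3/60 vs 6/60) | 0 to 3 | −5 points |
| 25% vs 5% (15/60 vs 3/60) | 0 to 15 | +20 points |

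The middle column depends on attribution alone. It overlaps across all three rows, although the true contrasts differ in sign.

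**Step 5: what a two-arm comparison could deliver.** After the protocol's 10% drop-out, 60 × 0.9 = 54 per arm are evaluable. Power (two-sided 5%, pooled variance) is Φ{[d√n − 1.96√(2p̄(1−p̄))] / √[p₀(1−p₀) + p₁(1−p₁)]}, where d = p₁ − p₀ and p̄ is the mean of the two rates.

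- 5% vs 25%: (0.20 × 7.348 − 1.96 × 0.505) / 0.485 = 0.99, power about 84%.
- 10% vs 30%: (0.20 × 7.348 − 1.96 × 0.566) / 0.548 = 0.66, power about 75%.
- 5% vs 15%: (0.10 × 7.348 − 1.96 × 0.424) / 0.418 = −0.23, power about 41%.

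With 10% in each arm, the 95% interval for the risk difference has half-width 1.96 × √(2 × 0.10 × 0.90 / 54) = 11.3 points. The comparison is feasible but imprecise for small differences. Trial status reports that recruitment closed before 120 were enrolled, so actual precision will be lower.

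**Step 6: a condition on the comparison.** Section {11c} describes weekly blood tests for the intervention arm only, for titration and adherence. If those samples also yield blood counts, anaemia and leukopenia could be found more often in that arm simply because it is tested more often. Counting events regardless of attribution does not remove this imbalance in detection.

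**The case against.** A reader might infer that the safety objective has no fair comparator at all. The documents do not support that. Section {16a} gives a concurrent 1:1 randomised control, section {22} records every adverse event without restriction by cause or arm, and item 7 adds safety measures not confined to sirolimus. Nothing rules out a between-arm table. This part of the defence stands in full: the defect lies in the stated outcome, not in the data.

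It can also be said that item 6 measures what it names. Cessation of and adherence to a newly started drug have no control counterpart, and describing them in one arm is normal. That also stands, and both should be kept as descriptive items.

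Next, drug-related may mean recognised sirolimus effects, with the six events as the list, and not events judged related one by one. Item 6 does not settle this. Under that reading the attribution problem falls away, but the outcome still concerns sirolimus only and the control rate is still unused.

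Finally, adverse event tables by arm and grade are commonly left to an analysis plan, which is not shown. That is right about tables and methods, and their absence is no finding. The point here is narrower. The article states an outcome, and an analysis plan that followed it faithfully would not estimate the contrast that the objective concerns.

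**Conclusion.** The point holds in limited form. Item 6 is a one-arm outcome expressed through drug-related events, in a trial with unmasked clinical staff and no masked attribution described. It does not use the randomised control or the all-cause data to answer the third objective. Item 7 closes the gap only for proteinuria, and only after vaccination.

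The size of any distortion cannot be computed, because no event rates are given; the counts above rest on assumed rates. The primary analysis is unaffected and no data are lost. The change is worth making, because the present wording would leave the tolerance conclusion dependent on attribution, but it is not a fundamental flaw. The conclusion rests on reading item 6 as written. A fuller protocol or analysis plan that already specifies an all-cause between-arm comparison would largely resolve it.

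**What to change.** Reword the safety and tolerance outcome as a comparison by randomised allocation:

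- All-cause adverse events by grade, and each of the six named events regardless of attributed cause, from randomisation to 7 days after the final visit.
- Risk differences with 95% confidence intervals.
- Anaemia, leukopenia and proteinuria counted only from assessment times common to both arms. Findings from the additional weekly intervention-arm tests are reported separately.
- Sirolimus cessation, sirolimus adherence and attributed relatedness kept as descriptive supplements.

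The cost is wording and a little more analysis. Section {22} already requires the adverse event data, so no new collection is needed for them. Restricting laboratory events to common times discards some intervention-arm findings from the main contrast. The intervals will be wide because recruitment closed short of 120, and the report should say so and not read a non-significant difference as evidence of equal safety.
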